### Blinding

Due to the nature of the interventions, instructors/teachers and participants will not be blinded to the intervention/control status during the intervention period. However, outcome assessors will be blinded to the intervention/control status of the subjects, except for measures of fidelity and motivation. Data analyst will be blinded to intervention/control status of the subjects.

### Outcome measurements

To evaluate the effect of the interventions, tests assessing reading related skills will be administered at the schools prior and post the 8-week intervention period by trained staff. In addition, a third data collection will be completed approximately three months after the cessation of the intervention period to evaluate potential retention effects. Primary outcomes assessing potential training effects include word reading (target words) and knowledge of trained letter-sound correspondences, while secondary outcomes assessing potential transfer effects include word reading (untrained words), letter fluency, general knowledge of letter-sound correspondences and word reading accuracy and speed. In addition, to explore potential mediators working memory, attention, intrinsic motivation, gross motor skills and fine motor skills will be assessed. At baseline, immediately post intervention and at three months follow-up, tests will be administered in groups and individually on two separate days. Compliance data will be collected following each session by the instructor/teacher and intrinsic motivation will be evaluated following four different sessions (week 2, 4, 6 and 8). All data will be collected during school hours which will ensure the children’s participation during data collection. In cases of absence on the day of scheduled data collection, children will be invited to complete the tests on another day.

#### Group tests

The group tests will be conducted in groups of 12–14 children in the classroom and will have a duration of approximately 60 min. During group testing, students will be placed with plenty of space between them to avoid copying.

##### Bogstaveprøve 2 [‘Letter test 2’]

This test has been widely used in the Danish school system. The test consists of two subtests assessing simple letter-sound knowledge and vowel identification, respectively. For the purpose of the present study, only the first subtest will be administered to assess standard letter-sound knowledge. The subtest will be administered strictly according to the manufacture’s description [43]. The subtest consists of 20 items (preceded by two practice items). Each item consists of a picture followed by five letters. The participants will be instructed to identify the first letter of the word illustrated by the picture. The word is read aloud by the instructor. Participants will be told to use a red pencil to mark the letters and use a blue pencil to mark if a mistake is made. The score is the number of items correct.

##### Ordlæseprøve 1 [‘Word reading test 1’]

As for letter test 2, this test is widely used in the Danish school system and will be administered strictly according to the manufacture’s description [42]. The test consists of 78 items (preceded by two practice items) and evaluates word reading accuracy as well as efficiency. In each item participants have to select one of four pictures that corresponds to a printed word. Words increase in length from two to four letters. Participants solve as many items as possible within a time limit of 4 min. Every minute children will be asked to change pencil color in order to monitor their progression throughout the test. The score is the number of correctly solved items (efficiency) and percentage of correctly solved items (accuracy).

##### Knowledge of trained letter-sound correspondences

To evaluate the children’s knowledge about letter-sound correspondences trained in the intervention and control period, a simple multiple-choice test has been constructed. The test consists of 15 trials. In each trial, a sound corresponding to a standard or a conditional pronunciation of a letter is said out loud by the assessor. Children are instructed to identify the correct letter matching the sound from a row of four letters. Before the test trials, children will be provided with one practice trial. The 15 sounds represent both standard and conditional pronunciations of the letters a, e, o, r, u and v (Table 2). Results are numbers of correct letter-sound correspondences.

##### Gross motor skills (flamingo balance test)

Gross motor skills including balance [9] has previously been linked to academic performance [10]. The flamingo balance test is a standardized test that assesses the ability to balance successfully on one leg [1]. The children will be asked to bend their free leg backwards and grasp the foot with their hand on the same side. Children are instructed to stand on one leg for 1 min. To become familiar with the test, children will be given one try before the actual test. The number of attempts needed to stand on one leg for 1 min will be counted for each leg. If a child put his/her foot down more than 15 times within the first 30 s of the test, the child will be excluded. Children will be provided with a badge showing their identification number. The test will then be recorded and analyzed afterwards. The test score is the sum of attempts with both legs; lower scores indicate better performance.

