##### Letter naming fluency

A test of letter naming fluency will be included, since the speed of letter naming has been associated with e.g. word recognition and reading fluency [45, 47, 64, 76]. This Danish version of the Letter Naming test is based on the same principles as DIBELS Letter Naming Fluency [30] and has previously been used to evaluate children’s ability to name letters [65]. The test consists of a piece of paper (A4) with 12 rows of 10 letters (mixed upper- and lower case). The child is asked to name as many letters as possible in 1 min while pointing to each letter. Wrong namings are registered by the assessor. If the child does not name the letter within 3 sec, the assessor says the name of the letter and encourages the child to name the next letter. If all 10 letters in the first row are named incorrectly, the test is discontinued. One row of 10 letters will be provided as practice. Result from the test is numbers of letters named correctly.

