### Plan for data analysis

In accordance with the Consolidated Standards of Reporting Trials (CONSORT) 2010 for randomized controlled trials [57], flow of participants will be reported. Descriptive statistics will be summarized across schools and classes for each group. Potential differences at baseline between subjects included and excluded in the analyses (e.g. drop-outs) as well as differences between groups at baseline will be tested. Further, compliance to the intervention will be summarized for each group. Intention-to-treat analyses will be performed to assess the effect of the intervention on primary as well as secondary outcomes. Multilevel mixed model will be used as this model is able to provide an unbiased estimate given missing data assuming data is missing at random conditional on variables included in the model [83]. Patterns of missing data will be investigated. To account for the cluster structure in the data (i.e. subjects within classes within schools), class and school will be included as random effects in the model. Due to the randomized design, which is used to ensure equal distribution of confounding variables between groups, we will only adjust for potential confounding variables (e.g. sex, age) which show unevenly distribution between groups at baseline. In addition, per protocol analyses will be conducted using above-mentioned approach including participants with a participation rate above 90%. In addition, structural equation models (SEMs) will be used for mediation analyses to explore potential mediators.

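### The Flamingo balance test excludes the worst balancers instead of scoring them, so an exploratory mediator is cut off at its poor end by its own value (minor)

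*Protocol article*

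**What the plan says.** The section on gross motor skills describes a one-minute balance task on each leg: "The number of attempts needed to stand on one leg for 1 min will be counted for each leg". The scoring is "The test score is the sum of attempts with both legs; lower scores indicate better performance". The section also sets the rule at issue: "If a child put his/her foot down more than 15 times within the first 30 s of the test, the child will be excluded". It assigns no value to such a child. It does not say whether the limit applies to each leg, or whether the child leaves this test, this visit or the dataset. Table 1 schedules the test at baseline, post-intervention and three months.

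The role of the score is given under Outcome measurements: "to explore potential mediators working memory, attention, intrinsic motivation, gross motor skills and fine motor skills will be assessed". The Plan for data analysis adds that "structural equation models (SEMs) will be used for mediation analyses to explore potential mediators". The same section plans to compare included with excluded subjects at baseline and to look at patterns of missing data.

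Other tests handle very poor performance differently. For letter naming, "If all 10 letters in the first row are named incorrectly, the test is discontinued", and the result is still a number of correct letters. Untrained word reading and digit span also stop early but remain counts. Nothing in those sections removes the child.

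**The concern.** A child who keeps losing balance has supplied a result, and it lies at the bad end of the scale. The rule turns that result into a missing value. Missingness then depends on the quantity being measured, and a poor balancer is likely to be missing at more than one visit, so the baseline score may not be there to help.

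If an intervention improves balance, fewer of its children meet the rule after treatment. More of the poor end is then removed from the control group than from the intervention group, which pulls the two scored groups together. The narrower range of scores also weakens the correlation between balance and reading. Both are paths in the planned mediation model. The planned comparison of included with excluded children and the review of missing-data patterns would describe the loss, but they would not restore the scores.

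**Working it through.** **Figures in the plan.** The document gives none for this test: no failure rate, no spread and no expected effect on balance. The sample-size figures do not bear on the point. Everything below therefore rests on stated assumptions.

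**Model.** Take the score as normal with SD 1 and higher meaning worse. Control children have mean 0, and an intervention arm has mean −d because all its children improve by d. A child above a cut c is excluded, and q is the share of control children above c. Write φ and Φ for the standard normal density and distribution function.

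- Mean of the scored children: m(μ) = μ − λ, with a = c − μ and λ = φ(a)/Φ(a).
- Variance of the scored children: 1 − aλ − λ².
- Mean if excluded children are scored at c instead: m(μ)Φ(a) + c[1 − Φ(a)].

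**Worked case, d = 0.25 and q = 10%.** The cut is c = 1.2816.

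- Control: λ = 0.1950, so the scored mean is −0.1950.
- Intervention: a = 1.5316, λ = 0.1317, so the scored mean is −0.3817. The share excluded is 6.3%.
- Difference with exclusion: 0.3817 − 0.1950 = 0.187, and 0.187/0.250 = 75%.
- Scored variances: 0.712 in control and 0.781 in the arm. With weights 2:1 the SD is 0.857, so the standardised difference is 0.187/0.857 = 0.218 against a true 0.250.
- Scored at the limit: control −0.0473, intervention −0.2773, difference 0.230, or 92%.

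**Correlation with reading.** Let u² be the variance ratio after exclusion. A true correlation r becomes ru/√(1 − r² + r²u²). With r = 0.30 (assumed) and u² = 0.712, this is 0.26.

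**Range for d = 0.25:**

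| Control children failing | Arm failing | Raw difference kept, excluded | Raw difference kept, scored at limit | Standardised difference after exclusion (true 0.250) | Correlation after exclusion (true 0.30) |
|---|---|---|---|---|---|
| 1% | 0.5% | 95% | 99% | 0.244 | 0.29 |
| 5% | 2.9% | 84% | 96% | 0.230 | 0.27 |
| 10% | 6.3% | 75% | 92% | 0.218 | 0.26 |
| 20% | 13.7% | 62% | 83% | 0.199 | 0.23 |
| 30% | 21.9% | 53% | 74% | 0.184 | 0.22 |

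With d = 0.5, exclusion keeps 96%, 86%, 78%, 66% and 56% of the raw difference.

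**Check closer to the actual rule.** The rule acts on the first 30 s, not on the total. Falls were therefore simulated as gamma-Poisson counts (shape 4) for two legs and two half-minutes. A child was excluded for more than 15 falls in the first half on either leg, and the arm had a 20% lower fall rate.

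- Failure 1.6% against 0.4%: 90% of the raw difference kept; standardised 0.365 to 0.357.
- Failure 7.5% against 2.8%: 71% kept; standardised 0.373 to 0.334.
- Failure 17.6% against 8.3%: 53% kept; standardised 0.379 to 0.298.

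**A case where the effect does not shrink.** Let the 0.25 SD benefit occur only in children below a cut that 10% exceed. The full difference is 0.225 and the difference after exclusion is 0.250. Attenuation is therefore the usual direction, not a necessary one.

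**The case against.** The strongest reply is that little hangs on this score. It is one of five candidate mediators and is neither a primary nor a secondary outcome. More than 15 foot-downs in 30 s is about one every 2 s, so the rule may catch very few children. At 1% failure only about 5% of the raw difference is lost, and standardised differences move less still. All of this stands, and it sets the severity.

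The protocol also calls the test standardised, and the rule may belong to that standard, which cannot be checked here. That could justify stopping the test. It does not make discarding the result harmless, because stopping and scoring are separate decisions.

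A reader might infer three stronger things that the document does not support.

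- *That the rule breaks the assumption behind the main analysis.* The sentence "assuming data is missing at random conditional on variables included in the model" justifies the mixed model, which follows directly from the intention-to-treat analyses of primary and secondary outcomes. Balance enters through the structural equation models, for which no missing-data assumption is stated. Nor is any change-score or lagged analysis of balance specified.
- *That the rule alone could produce a null mediation finding.* Even at 30% failure, 53% of the raw difference remains, and a correlation of 0.30 falls to 0.22. That is attenuation, not a null.
- *That the child leaves the trial.* The section on participants does use exclusion to mean removal from the final dataset. But this sentence sits inside one test's description, and removal after randomisation would conflict with the intention-to-treat plan. The wording needs clarifying; it is not evidence of intent.

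**Conclusion.** The point holds and is minor. As written, the rule cuts off the exploratory gross-motor mediator at its poor end by its own value, and nothing else in the document gives those children a score. If balance improves in all children of an intervention arm, the arm effect on this score and its correlation with reading would usually be understated. The loss is about 5% of the raw difference at 1% failure and about a quarter to a half at 10% to 30%.

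These sizes assume a normal score and a uniform 0.25 SD shift, and the failure rate is unknown. That either intervention changes balance is itself an assumption, since the protocol predicts no such effect. Estimates for the reading outcomes do not change as long as the excluded child stays in the dataset.

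**What to change.** Add to the description of the test:

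- Only the Flamingo test stops. The child stays in all other tests and analyses. Say whether the limit applies to each leg.
- A child who meets the rule receives a fixed worst or limit score for that leg, set in advance and not derived from the observed data, or the score is treated as right-censored. Because the rule looks only at the first 30 s, a child who completes the minute can still collect more than 16 attempts. The fixed value should therefore not fall below scores that completers can reach.
- A rank-based or censored analysis serves as a check.
- The number of children who meet the rule is reported by arm and visit.

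The cost is a few sentences and no new data, since the test is recorded and scored afterwards. A fixed score does not need a full-minute count, which would be lacking if the test is stopped. The downsides are a ceiling in the score, which the rank-based or censored analysis addresses, and possibly less comparability with other uses of the test.

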#### Individual tests

The individual tests will be conducted in a quiet room with one assessor and take maximum 35 min for each participant to complete. All tests will follow standardized procedures. Initially, the assessor will fill out a form with background information about, e.g. date of testing, sex, dominant hand, bilingualism etc.

##### Word reading with pictures (target words)

During the intervention period, all children will study certain words (*target words*) thoroughly. To evaluate the specific effect of the intervention on children’s ability to read the target words, a computer-based test has been constructed. This word reading test consist of 18 presentations of targets words; one target word per presentation. Below the target word are placed four pictures of which one illustrates the target word. For the children to give a correct answer, they will have to touch the picture matching the target word on the touch screen. They are asked to touch the correct picture as fast as possible. The three remaining pictures represents words (distractors) that have either the initial (two pictures) or the final (one picture) sound in common with the target word. The presentations of target words and the order of the four pictures are randomized between subjects and time points. During the test, children are allowed to ask questions concerning the pictures (e.g. *what is shown on this picture?*) but not regarding the target word (e.g. *what is the sound of this letter?*). The results from the test constitute mean response time for correct answers and number of correct answers.

##### Word reading without pictures (untrained words)

To test the potential transfer effects of the intervention on children’s ability to read small words, a computer-based test *not* including the target words has been constructed. This test consists of 12 presentations of untrained words; one word per presentation. The 12 words consist of four 2-letter words, four 3-letter words and four 4-letter words. Two versions of the test will be completed; one conducted at baseline and one at post intervention in a randomized and counterbalanced order. The two versions are matched carefully on letter sounds, numbers of letters and assumed difficulty. Pilot testing demonstrates no significant difference between performances in the two versions of the tests. Within each version of the test and within words with the same number of letters, words are presented in a randomized order. The child is instructed to read the word and say it aloud while looking at the assessor. Then the assessor registers the answer as correct or incorrect by pressing a green or red button, respectively. This procedure allows the child to read the word aloud for itself before providing an answer to the assessor. Each word will be presented for 16 s; providing the child with 15 s to get an answer registered (1 s is required for the assessor to register an answer). If no answer is given within the time limit, a new word will appear on the screen. If incorrect or no answer is provided for *all* four 2-letter words, the test is discontinued. The outcome is the number of correctly read words.

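### Test version is set by design for the untrained-word outcome, but the covariate rule, read literally, leaves it out of the model, so any version gap stays as avoidable residual noise (minor, precision only)

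*Protocol article*

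**What the plan says.** All references are to the protocol article.

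- **Outcome measurements** gives the test its rank: "secondary outcomes assessing potential transfer effects include word reading (untrained words", among others. It is not a primary outcome.
- **Word reading without pictures (untrained words)** describes a 12-word test. On scoring: "The outcome is the number of correctly read words". On the versions: "Two versions of the test will be completed; one conducted at baseline and one at post intervention in a randomized and counterbalanced order". On how they were built: "The two versions are matched carefully on letter sounds, numbers of letters and assumed difficulty". On the evidence that they are alike: "Pilot testing demonstrates no significant difference between performances in the two versions of the tests". No pilot size, estimate or interval is given.
- **Plan for data analysis** specifies a multilevel mixed model in which "class and school will be included as random effects in the model". On covariates it says that "we will only adjust for potential confounding variables (e.g. sex, age) which show unevenly distribution between groups at baseline". Test version is not mentioned.

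**The concern.** Matching on assumed difficulty and a non-significant pilot are reasonable precautions, but neither shows that the versions are equally hard. If they differ, half the children meet the easier version first and half meet it last. Individual gains are then pushed up in one half and down in the other by the size of the gap.

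Because the order is randomised, this does not favour any arm. It does add spread to the scores. The spread is fully explained by a variable the trial itself sets, so a model that includes version removes it.

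The covariate rule works against this. It selects variables by imbalance between arms, and a counterbalanced version will normally look balanced. At stake is some precision, and so some power, for the whole-body versus control, hand versus control and whole-body versus hand contrasts on one secondary outcome.

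**Working it through.** **The plan's own figures.** The article gives no figure for a version gap, so there is none to reproduce on this point. The group sizes come from the sample size section: 53, 53 and 106, total 212, and 212/0.8 = 265 recruited. The starting figure of 158 reproduces as a three-group F test with Cohen's f = 0.25 (power 80.2%).

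**Assumptions, because the article is silent.** Version gap d of 0.1 to 0.5 SD of a single score; pre-post correlation ρ = 0.7, with 0.5 and 0.8 as a check; post score analysed with adjustment for baseline.

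**Step 1: what a pilot can miss.** Chance that a two-sided 5% paired t test is non-significant when the same children read both versions:

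| True gap, between-version correlation | n=10 | n=15 | n=20 | n=30 |
|---|---|---|---|---|
| 0.5 SD, 0.7 | 55% | 36% | 22% | 7% |
| 0.5 SD, 0.5 | 71% | 56% | 44% | 25% |
| 0.3 SD, 0.7 | 80% | 71% | 62% | 46% |

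The table shows what non-significance leaves open. It does not show that a gap exists.

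**Step 2: noise added if version is left out.** Code version as ±d/2, with opposite signs at the two occasions. With slope ρ on baseline, the residual variance is 1 − ρ² = 0.51.

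- Gap present at both occasions: added variance (d(1+ρ)/2)².
- Gap hidden at baseline by floor effects: added variance (d/2)².
- Loss of effective sample size: 1 − 1/(1 + added/0.51).

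| d (SD) | Added, both occasions | Loss | Added, post only | Loss |
|---|---|---|---|---|
| 0.1 | 0.0072 | 1.4% | 0.0025 | 0.5% |
| 0.2 | 0.0289 | 5.4% | 0.0100 | 1.9% |
| 0.3 | 0.0650 | 11.3% | 0.0225 | 4.2% |
| 0.5 | 0.1806 | 26.2% | 0.0625 | 10.9% |

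Example at d = 0.3, both occasions: (0.3 × 1.7/2)² = 0.0650; 0.0650/0.51 = 0.1275; 1 − 1/1.1275 = 11.3%. With the gap at both occasions, ρ = 0.5 gives 2.9%, 6.3% and 15.8% at gaps of 0.2, 0.3 and 0.5 SD; ρ = 0.8 gives 8.3%, 16.8% and 36.0%.

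**Step 3: power.** For 53 versus 106 and an assumed effect of 0.5 residual SD (0.5 × √0.51 = 0.36 SD of the score), the normal approximation gives 0.5 × √(53 × 106/159) = 2.97 and a power of 84.4% with version in the model. With version left out and the gap at both occasions, power is 82.4%, 79.9% and 72.4% at gaps of 0.2, 0.3 and 0.5 SD. Dividing 2.97 by the square root of the post-only inflation gives 83.7%, 82.9% and 80.1%.

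**Step 4: validity.** In 4,000 simulated trials per setting (ρ = 0.7, version omitted), the estimates were within 0.007 SD of zero. The type I error was 4.4% at a 0.3-SD gap and 4.6% at 0.5 SD. The SD of the estimate rose from 0.120 with no gap to 0.125 and 0.139. The cost is precision alone.

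**The case against.** The strongest reply is that the design already deals with this. The versions are matched, piloted and given in randomised, counterbalanced order, which is what one does when equality is not taken for granted. A reader might infer that the protocol treats the versions as interchangeable on the strength of the pilot, or that the arm comparison is biased. The text supports neither: the pilot is one of three safeguards, and randomised order protects the contrasts. This part of the reply stands in full.

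Second, the covariate rule speaks of confounders such as sex and age. A randomised test version is a design factor, so its exclusion is an inference, and an analysis plan not shown may include it. The rule does not name the baseline score either, although the sizes above assume baseline adjustment. This stands in part. The word *only* is restrictive, and class and school are the only other terms named. An analyst following the sentence as written would leave version out.

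Third, the sizes are assumed and may be too large. The article says that few children can read words at the start of Grade 0, and the test stops if all four two-letter words fail. Many baseline scores may therefore be near zero on either version. This stands, and it is why the post-only figures form the lower end of each range.

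Finally, the missing pilot size and interval are details that an article may leave out, and are not counted as a fault here.

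**Conclusion.** The point holds as a minor, free improvement. A non-significant pilot does not show equal difficulty, and the covariate rule taken at its word leaves a design-set factor in the residual of one secondary outcome.

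Under the assumptions of ρ = 0.7 and baseline adjustment, the loss of effective sample size is about 2-5% at a 0.2-SD gap, 4-11% at 0.3 SD and 11-26% at 0.5 SD, and negligible at about 0.1 SD. Nothing in the article shows that a gap exists. It would be going too far to say that the transfer result is biased, that its error rate is inflated, or that power has in fact been lost.

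**What to change.** In the model for untrained-word reading, pre-specify the version read at each occasion as a fixed effect, regardless of balance between arms, and state it as an explicit exception to the covariate rule in the plan for data analysis.

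The form matters. In a longitudinal mixed model, a main effect of version order (A then B, or B then A) does not remove the gap: it enters as +d/2 at one occasion and −d/2 at the other and averages to zero within each order. There, use version per occasion or, equivalently for the two occasions, order-by-time. Version order as a main effect is enough only in a baseline-adjusted model of the post score.

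Table 1 also schedules this test at the 3-month follow-up, while the test description assigns versions only to baseline and post. The version used at follow-up should be recorded, so that the same term can be applied there.

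The cost is one sentence and about one degree of freedom. Apart from keeping the version on record, no extra data, children or tests are needed.
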